### Intervention: Sleep Stabilization

Participants will be instructed to start following an assigned sleep schedule the morning after visit 3. Similar to the light treatment intervention, the assigned wake time will be their average final wake time as determined during the baseline week, or up to 1 hour earlier than their average wake time. If the participant’s assigned wake time is advanced from their average wake time, then their bedtime will also be shifted earlier to avoid sleep deprivation. Participants will also be instructed not to sleep or meditate (closing eyes) within 5 hours after their assigned wake time, to avoid creating a morning dark pulse that may shift circadian timing.

Adherence will be assessed via actigraphy data measured by the Fitbit Charge 5 or 6, which will be reviewed with participants at the weekly study visits by unblinded staff. Research staff will contact all participants via phone call or text 10 minutes after their assigned wake time each morning to ensure that they are awake and out of bed. Participants will also be provided an alarm clock set to their assigned wake time to promote adherence.

### Comparator: Treatment as Usual

Participants assigned to TAU will be instructed at visit 3 to follow their usual ad lib sleep schedule, as they did during the baseline week. Research staff will contact these participants via phone call or text each day to encourage them to complete their daily logs. This contact, together with the weekly study visits, will ensure equivalent study contact and attention between the morning light treatment group and the TAU group. The TAU participants' wrist actigraphy data will also be reviewed weekly during the Zoom visits, with feedback on following the study procedures.

### Outcome Measures

Study outcomes will be assessed in each group at pretreatment (visit 3), posttreatment (visit 7), and then at a follow-up 3 months after posttreatment (visit 8) to evaluate the duration of any changes in each treatment condition. The study assessment schedule is shown in Table 1.

### Self-Reported Outcomes

The primary outcome measure is the FIQR [48]. The FIQR consists of 21 items that assess function, overall impact, and symptoms. Total scores range from 0 to 100, with higher scores representing worse functional status. The secondary outcome measure is the Brief Pain Inventory (BPI), which assesses for the presence of pain, pain intensity, and functional interference from pain [53]. The BPI consists of 2 scores (pain severity and pain interference) with higher scores indicating more pain or greater pain interference. The BPI has been validated for fibromyalgia specifically [54,55].

Three additional outcome measures will be explored as potential mediators. The Patient Health Questionnaire-9 (PHQ-9) is a reliable measure of the severity of depressive symptoms [56]. The PHQ-9 consists of 9 items, and higher scores reflect higher levels of depressive symptoms. The Patient-Reported Outcomes Measurement Information System (PROMIS) Sleep Disturbance Short-Form 8b is a reliable measure of sleep quality [57]. Higher scores on the PROMIS Sleep Disturbance Short-Form 8b reflect worse sleep quality. The Morningness-Eveningness Questionnaire (MEQ) [58] will be used as a proxy marker of circadian timing. The MEQ score correlates well with the gold standard circadian phase marker, the dim light melatonin onset [59], and significantly increases towards more “morningness” after 13-28 days of a morning light treatment [60]. This will allow us to confirm an expected phase advance or earlier shift in circadian timing in response to morning light treatment.

### Social Determinants of Health Measures

At visit 1, an SDOH index score will be derived from individual and community-level data consistent with previous publications [61,62]. Individual-level data collected will include education, household income (and number of individuals in household to assess poverty level), marital or partner status, employment, and medical insurance status. Community-level data will also be assessed with the national Area Deprivation Index (ADI) percentile, derived from each participant’s full address. Each SDOH factor will be scored 0 for protective or 1 for risk, determined by evidence-based ranges and then summed to calculate an SDOH Risk Index score (0 indicating no risk to 6 indicating high risk). This approach accounts for the additive burden of numerous SDOH variables [63]. The following SDOH factors will be coded as 1 for high risk: (1) education up to and including high school (beyond high school is protective [64]); (2) household income below US Federal Poverty guidelines (above is protective [65]); (3) no marital or partner is a risk (presence of a partner is protective [66]); (4) being unemployed, disabled, a student or homemaker is a risk (being employed or retired is protective [67]); (5) no medical insurance is a risk (having medical insurance is protective [68]); (6) ADI percentile >80% is a risk (≤80% is protective [69]).

We will also collect three measures at study start (visit 2) to explore their utility when examining symptom burden, adherence, and treatment outcomes. These measures include the Experiences of Discrimination (EOD) questionnaire, which is a self-report measure that assesses how often people feel they have experienced unfairness on the basis of race, ethnicity, gender, age, religion, physical appearance, sexual orientation, or other characteristics [70]. Scores range from 10-60, with higher scores indicating greater lifetime discrimination. Participants will also be asked to complete the Multidimensional Scale of Perceived Social Support questionnaire, which is a self-report measure that assesses an individual’s perceived level of social support with family, friends, and significant others [71]. Scores range from 0-72, with higher scores indicating a greater perceived level of social support. The third measure will be the Centers for Disease Control’s Social Vulnerability Index (SVI) derived from each participant’s full address. The SVI is a more recently available community-level variable and incorporates census variables to identify vulnerable communities within counties based on 15 factors organized within 4 themes: SES, household composition, ethnicity/race/language, and housing transportation [72]. Higher values indicate greater vulnerability.

### Additional Measures

At study start (visit 2), after eligibility is determined, participants will complete several questionnaires to characterize the sample. The Cambridge-Hopkins questionnaire [73] will assess for restless leg syndrome (RLS). For those who screen positive, the severity of RLS will be determined with the validated patient-report International Restless Leg Syndrome study group severity rating scale [74]. This scale assesses symptoms over the past 7 days, and the total score ranges from 0 (no symptoms) to 40 (very severe symptoms). Patients who do not screen positive will be assigned a severity score of 0. The severity score will be used as a moderator in the statistical analysis (see below). Participants will also be assessed for obstructive sleep apnea (OSA) with the STOP-BANG questionnaire [75]. This questionnaire assigns a point for each symptom or risk factor, and this score will also be used as a moderator in the statistical analysis. The Positive and Negative Affect Schedule (PANAS) questionnaire [76] will assess for trait positive and negative affect, and will be used to derive predisposing dispositional traits (protective or vulnerable) [77]. These traits will also be examined as a potential moderator in the statistical analyses. Finally, participants will also complete two brief questionnaires about their study expectations at visit 3, after they are informed of the condition they have been randomized to, and a study satisfaction questionnaire at visit 7.

Participants will wear the Fitbit Charge 5 or 6 on their non-dominant wrist to monitor activity and sleep. The Fitbit Charge uses accelerometry and cardiac autonomic signals to estimate sleep and has been compared to gold-standard polysomnography, demonstrating differentiation of sleep and wake states superior to US Food and Drug Administration cleared actigraphy [78]. We will export data from the Fitbit Charge in 30-second intervals using the Fitabase software. To augment the sleep data collected by the Fitbit device, sleep diaries will be completed, and participants will text a research email account to identify when they are trying to fall asleep (bedtime) and at their final wake time. Bedtime and rise time data through the time-stamped text messages will allow for confirmation of correct sleep onset and offset and calculation of total sleep time, wake after sleep onset, and sleep efficiency [79]. These objective sleep parameters will be primarily used to verify participant adherence to the morning light treatment and sleep timing stabilization schedule, but will also be examined for group differences. Participants will also track their daily use of caffeine, alcohol, medications, exercise, and psychotherapy on a daily event log.

### Safety Measures

At each weekly visit after the start of treatment (visits 4-7), participants will complete a self-reported measure of physical and emotional symptoms they have experienced in the past week using the Systematic Assessment for Treatment Emergent Events (SAFTEE) as we and others have used in previous light treatment trials [37,52,80]. Unblinded research staff will assess the severity of symptoms and their relevance to the study and assigned group, to ensure no significant negative effects are associated with the study participation. If severity meets a pre-determined threshold based on SAFTEE, the unblinded research staff will alert an unblinded study physician to further assess the participant’s safety and risk for an adverse event. In addition, at each weekly visit and 3-month follow-up, suicide risk will be assessed using the Columbia Suicide Severity Rating Scale (C-SSRS) [81], and during weekly visits, mood worsening will be examined with the Beck Depression Inventory (BDI) [82]. At least annually, an independent safety monitor will review the reported side effects and confirm it is safe to continue the study.

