## Introduction

Chronic nociplastic pain includes conditions such as irritable bowel syndrome, interstitial cystitis, and the quintessential nociplastic pain condition, fibromyalgia, which alone affects more than 20 million Americans [1]. While the mechanisms underlying nociplastic pain are not completely understood, central nervous system–mediated amplification of pain and other sensory input, along with altered pain modulation, play a major role [2]. In addition to pain, mood and sleep disturbances, fatigue, and cognitive symptoms are common [3,4]. Resultant disability, lost productivity, and poor quality of life have profound costs at the individual and societal level [5]. Underserved individuals experience these impacts more profoundly [6] as symptom burden is heavily influenced by demographic risk factors, including social determinants of health (SDOH: eg, education, income, medical insurance, and community resources) [7-10].

While a pharmacological approach has traditionally been the first line of treatment for fibromyalgia, drug therapies offer only small benefits [11-14] and result in a high rate of discontinuation due to adverse effects [11]. Newer national guidelines suggest that the initial approach to the treatment of fibromyalgia consists of non-pharmacological interventions [15-17]. Physical therapy, exercise, and psychological therapies such as cognitive behavioral therapy (CBT) have demonstrated efficacy but can be difficult to access in terms of cost and availability [18-20], and engagement can be problematic [21]. Indeed, individuals with chronic pain are most adversely impacted by SDOH, have the least access and ability to consistently engage in nonpharmacological therapies [7]. Thus, a need exists to develop novel adjunctive approaches to manage fibromyalgia symptoms that have optimal treatment effects, minimal side effects, and are easy to implement and readily accessible for all.

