Morning bright light treatment is a promising option for improving fibromyalgia symptoms. Meta-analyses have confirmed that morning light treatment improves mood (reduces nonseasonal depression) with medium effect sizes similar to those observed with pharmacological antidepressants [22,23]. Similarly, a meta-analysis indicated that morning light treatment improves sleep with medium effect sizes [24]. Improvements in mood and sleep are well-recognized as contributing to improvements in chronic pain [25,26]. Morning bright light treatment also advances circadian timing (shifts circadian timing earlier toward “morningness” [27]). As later circadian timing (“eveningness”) is associated with worse fibromyalgia pain [28,29], circadian phase advances associated with morning bright light treatment may help reduce symptoms (see Figure 1). In addition, emerging research in rodent models suggests green light exposure to be antinociceptive [30,31]. Importantly, while light treatment is associated with some side effects (headache, eyestrain, nausea, and agitation [32]), these symptoms often spontaneously remit [32,33], and patients rarely discontinue treatment due to these side effects [33]. Furthermore, light devices with a UV filter are considered safe with no changes in ophthalmologic examinations observed after 6 years of daily use (in fall and winter months) [34].

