**Safety Measures**																					
	C-SSRS^g^ (past 6 months)			✓																	
	C-SSRS (since last visit)					✓			✓		✓		✓		✓		✓		✓		
	BDI^h^					✓			✓		✓		✓		✓		✓				
	SAFTEE^i^										✓		✓		✓		✓				

^a^CHQ: Cambridge Hopkins Questionnaire.

^b^sIRLS: self-administered International Restless Legs Syndrome Severity Rating Scale.

^c^FIQR: Fibromyalgia Impact Questionnaire—Revised.

^d^BPI: Brief Pain Inventory.

^e^PHQ-9: Patient Health Questionnaire—9.

^f^PROMIS: Patient-Reported Outcomes Measurement Information System.

^g^C-SSRS: Columbia Suicide Severity Rating Scale.

^h^BDI: Beck Depression Inventory.

^i^SAFTEE: systematic assessment for treatment emergent events.

Eligible participants will be enrolled in the study at visit 2, during which questionnaires to characterize the sample will be completed (Table 1). Before visit 2, participants will be randomized to the morning light treatment, sleep stabilization treatment, or TAU group, and will be mailed the appropriate study supplies (see below for more details). All participants will receive a Fitbit Charge 5 or 6 to wear on their nondominant wrist to track their sleep and activity throughout the 5-week study protocol, along with daily logs to report their subjective experience of sleep and caffeine, alcohol, and medication use. A week later, at visit 3, pre-treatment outcome assessments will be administered, and treatment expectations will be assessed. The randomly assigned treatment condition will then begin the morning after visit 3. Thereafter, there will be weekly visits (visits 4, 5, and 6) to review each participant’s adherence to instructions (sleep timing alone or paired with the use of the Re-timer, depending on treatment group) and to systematically assess side effects (all groups). At visit 7, posttreatment outcome measures will be administered, and study satisfaction will be assessed. Participants will be required to abstain from alcohol and cannabis use within 24 hours of visits, with reminders the day before each visit.

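### No pre-treatment SAFTEE is scheduled, so for complaints without another baseline measure, pre-existing symptoms cannot be separated from new or worsened ones

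*Protocol article*

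**What the plan says.** The protocol article's Safety Measures section has SAFTEE completed "At each weekly visit after the start of treatment (visits 4-7". The SAFTEE row of Table 1 has four ticks, at visits 4, 5, 6 and 7. Procedures and Assessments sets the start of treatment: "The randomly assigned treatment condition will then begin the morning after visit 3". Every SAFTEE therefore falls after treatment has begun.

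The form is described as a "self-reported measure of physical and emotional symptoms they have experienced in the past week". On interpretation, Safety Measures says: "Unblinded research staff will assess the severity of symptoms and their relevance to the study and assigned group". A severity threshold, set in advance but not shown, brings in an unblinded physician. The weekly visits are also "to systematically assess side effects (all groups", so treatment as usual (TAU) and sleep stabilization are assessed in the same way as light.

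Two other safety measures do have pre-treatment values: in Table 1 the BDI and the C-SSRS are given at visits 2 and 3 and again at visits 4 to 7.

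**The concern.** The Introduction names the side effects of light as "headache, eyestrain, nausea, and agitation". It also describes a population with a broad symptom load: "In addition to pain, mood and sleep disturbances, fatigue, and cognitive symptoms are common". Entry requires an FIQR of at least 31. Some participants may well have had non-specific complaints in the week before treatment, and the schedule does not record which ones.

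A report of nausea at visit 4 may then be long-standing, new or worse, and SAFTEE cannot tell which. The only stated means of sorting such reports is a judgement of relevance by staff who know the arm and have no earlier SAFTEE value to compare with. That judgement could differ between arms.

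The low side-effect burden of light is part of the article's case for it (abstract Conclusions, Introduction, Discussion), so the quality of these data matters. An analysis plan cannot repair the gap later, because a baseline that was not collected cannot be recovered.

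**Working it through.** **What the article supplies.** It gives no side-effect rate, no background prevalence and no power figure for SAFTEE, so there is no stated figure to reproduce on this point. The 103 completers per arm come from Statistical Power and Analysis. That section's 80% does reproduce: the effects 0.47, 0.16 and 0.05 have mean 0.2267, so the noncentrality is 103 × 0.09487 = 9.77, and the F test on 2 and 306 degrees of freedom has power 80.2%. This concerns FIQR only.

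**Assumptions for the illustration.** Let b be the share who have the symptom before treatment, taken as 10%, 30% and 50%. Among those free of it, new onset is 5% under TAU and 20% under light. A pre-existing symptom persists and is reported again.

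**Formulas.**
- Raw any-symptom risk: b + (1 − b) × q, with q = 0.05 (TAU) or 0.20 (light), n = 103 per arm.
- New onset among those symptom-free at baseline: 0.05 v 0.20, n = 103 × (1 − b) per arm.
- Power, two-sided 0.05: Φ(|difference| / SE − 1.96), with SE = √[(p₀(1 − p₀) + p₁(1 − p₁)) / n].

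**One case in full, b = 30%.**
- Raw: TAU 0.30 + 0.70 × 0.05 = 0.335; light 0.30 + 0.70 × 0.20 = 0.440. Ratio 1.31. SE = √[(0.2228 + 0.2464) / 103] = 0.0675. Power = Φ(0.105 / 0.0675 − 1.96) = Φ(−0.40) = 34%.
- Symptom-free: n = 103 × 0.70 = 72.1. SE = √[(0.0475 + 0.16) / 72.1] = 0.0536. Power = Φ(0.15 / 0.0536 − 1.96) = Φ(0.84) = 80%.

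**Results, 103 per arm.**

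| Background b | Raw TAU v light | Raw ratio | Raw power | New-onset ratio | New-onset power |
|---|---|---|---|---|---|
| 10% | 14.5% v 28.0% | 1.93 | 67% | 4.0 | 89% |
| 30% | 33.5% v 44.0% | 1.31 | 34% | 4.0 | 80% |
| 50% | 52.5% v 60.0% | 1.14 | 19% | 4.0 | 66% |

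**Cross-checks.**
- The absolute difference over all 103 per arm is (1 − b) × 15 points, that is 13.5, 10.5 and 7.5, whether or not a baseline is taken. Only the noise around it changes.
- Counting new onset over all 103 per arm, with a pooled null variance, gives 87%, 76% and 61%, against 66%, 34% and 19% raw.
- Pre-existing symptoms make up b / (b + (1 − b) × 0.05) of TAU participants reporting the symptom: 69%, 90% and 95%.
- With all 130 enrolled per arm, raw power is about 77%, 42% and 23%, against 94%, 88% and 76% among the symptom-free.

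**The case against.** Four points can be made for the plan.

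**Randomisation protects the comparison.** All three arms complete the same form, so background symptoms should balance and the absolute excess under light is unbiased. This stands. The loss is in precision, in the size of the ratio and in attribution for the individual participant.

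**Other baselines exist.** The BDI is given at visits 2 and 3; the FIQR, which includes symptoms, at screening and visit 3; the PHQ-9, BPI and PROMIS Sleep Disturbance at visit 3. Medical history is taken, and light-triggered migraine and several eye conditions are excluded. This stands in part: mood, pain and sleep have a reference value, but the article shows none for nausea, eyestrain or agitation as such.

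**No between-arm test of side effects is stated.** SAFTEE is presented as monitoring with escalation, so the power figures describe a comparison that the article does not commit to. This also stands, and they are an illustration only. Raw rates and individual attribution remain hard to interpret even in a purely descriptive report.

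**The dilution depends on background rates that the article does not give.** The side effects it names for light are not the symptoms it lists as common in fibromyalgia, and a complaint that is rare at baseline loses little.

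A reader might go further and infer that long-standing symptoms will be counted as treatment-emergent, or that they will set off the alert threshold. The article supports neither: it states no counting rule, and the threshold is not shown. Nor does it support saying that no symptom at all can be classed as new or worsened, given the measures above.

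**Conclusion.** The point holds in a limited form. SAFTEE has no pre-treatment value, so for complaints without another baseline measure the trial cannot separate pre-existing from new or worsened symptoms, except through staff who know the arm. The between-arm absolute difference is not biased.

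Under the assumed rates, a true fourfold effect shows as a ratio between 1.93 and 1.14, and power is lower by about 22 points (89 − 67) at 10% background and 47 points (66 − 19) at 50%. The direction holds for any background above zero; the size rests on assumed prevalence and onset rates. It also rests on pre-existing symptoms persisting and on ignoring severity grades. The gain shown is for new onset only; a definition that includes worsening was not modelled.

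This is worth changing because it is cheap and cannot be recovered afterwards. It does not touch the FIQR analysis.

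**What to change.** Administer SAFTEE once at visit 3, with the other pre-treatment measures and before the participant is told the arm, so that it covers the ad lib baseline week. Visit 2 is an acceptable alternative. Define a treatment-emergent symptom as one that is new or increased in severity from that value, and compare arms on it. Keep the any-symptom comparison over all randomised participants alongside. The existing escalation and physician-review procedure need not change for this purpose.

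The cost is one short self-report form at a visit that already takes place. There are two limits:
- Supplies matched to the arm are mailed before visit 2, so some participants may guess their assignment. The answers would still precede treatment.
- By mid-July 2025, 55 of 390 were enrolled, leaving 390 − 55 = 335 who could still have had a baseline at that date. Those already treated lack one and enter only the any-symptom comparison. The report should say so and give the number with a baseline in each arm.

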### Statistical Power and Analysis

We plan to enroll 390 individuals, aged 18 years or older, who meet the 2016 revised diagnostic criteria for fibromyalgia [45] and have at least mild fibromyalgia symptoms (FIQR score of ≥31) [48] (see Textbox 1). We aim for 309 participants with complete data (103 per each of the 3 groups), assuming 20% attrition during the 5-week study period. The sample size will provide 80% power to detect a difference in the standardized effect sizes (changes from baseline to post-treatment) of 0.47, 0.16, and 0.05 in FIQR in morning bright light treatment, sleep timing stabilization, and TAU groups, respectively, with a two-tailed 0.05 level 1-way ANOVA test. The effect size in the morning bright light treatment group is clinically meaningful and detectable based on our previous study [37]. The effect size in the sleep timing stabilization arm is 1/3 of that in the morning bright light group, and we conservatively estimated an effect size of 0.05 in the TAU group due to study participation. The study should also have adequate power to detect a binary outcome of clinically meaningful improvement (≥30% from baseline) or achieving a treatment response (≥16.8 decrease in FIQR) [83].

We will conduct an intention-to-treat analysis. We will report descriptive statistics of the data and visually explore the summary statistics by group at each visit. We will analyze both primary and secondary outcomes using a mixed-effects longitudinal data model with participants as random intercepts to account for between-participant variability. Predictors will include post-randomization time, two intervention group indicators with TAU as the referent group, and the interactions of time by group indicators. We will examine the extent and pattern of key missing outcomes data, and if missingness is greater than 15%, we will use logistic regression to assess baseline characteristics predictive of missingness postrandomization and will include those baseline characteristics as covariates in the final model. While FIQR scores will be examined as a continuous variable, we will also examine the proportion of participants who show clinical response (a binary outcome of clinically meaningful improvement (≥30% from baseline) or achieving a treatment response (≥16.8 decrease in FIQR [83]) and analyze the binary outcome variable using a generalized linear mixed model with logit link. We will also explore the severity of restless leg syndrome, obstructive sleep apnea, dispositional trait, and biological sex as potential moderators of any treatment effects.

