**Figure 1 figure1:**
[figure not shown]
A conceptual model illustrating that morning bright light treatment, which is known to improve mood and sleep and to shift circadian timing earlier, has the potential to improve fibromyalgia. The measure used to assess each domain is shown in italics: Patient Health Questionnaire (PHQ-9), Morningness-Eveningness Questionnaire (MEQ), PROMIS Sleep Disturbance 8b, Fibromyalgia Impact Questionnaire–Revised (FIQR), and Brief Pain Inventory (BPI).

To date, only 3 studies have tested light treatment in people with fibromyalgia. In our first study, we tested 6 days of either a 1-hour evening or 1-hour morning bright light treatment in 10 participants with fibromyalgia [35]. Only the morning bright light treatment led to clinically meaningful improvements in function (>14% reduction in baseline Fibromyalgia Impact Questionnaire—Revised [FIQR] score [36]). In this study, we travelled to participants’ homes to set up white light boxes, which was burdensome for participants and staff. This experience led us to switch to a novel commercially wearable light device (Re-timer), which permits ambulation while receiving light from green LEDs positioned below the eyes. Our second study was a randomized clinical trial that tested 4 weeks of a 1-hour daily morning light treatment (bright or dim) using the Re-timer in 60 people with fibromyalgia [37]. We found that both groups responded to the morning light treatment, with clinically meaningful improvements in the FIQR (mean decrease of 11.2, *P*=.003). The findings were similar to those seen after exercise and were double those seen with CBT or analgesics (meta-analysis [38]). A third study by Martin et al [39] tested 7-9 weeks of a 1-2 hour daily white versus green light treatment in 21 people with fibromyalgia. The light was generated from LED strips, and the time of day of light exposure was not reported. They found that only the green LED light led to significant reductions in pain intensity, and quality of life and self-reported function also improved. Overall, morning bright light treatment is well-positioned to be a potentially accessible and scalable nonpharmacological treatment for fibromyalgia with minimal side effects. Furthermore, light treatment devices are commercially available, and light treatment can be self-administered at home, allowing easy access and dissemination once efficacy is established.

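### The stated adequate power for the binary FIQR response does not follow from the plan's own sizing: with normal change scores it is at most about 60% (three-group test) or 67% (light vs TAU)

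*Protocol article*

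**What the plan says.** All of this is in the Protocol article, Statistical Power and Analysis.

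- Sample size: "We aim for 309 participants with complete data (103 per each of the 3 groups), assuming 20% attrition during the 5-week study period".
- Sizing claim: "The sample size will provide 80% power to detect a difference" in "standardized effect sizes (changes from baseline to post-treatment) of 0.47, 0.16, and 0.05 in FIQR" for light, sleep stabilization and TAU respectively, "with a two-tailed 0.05 level 1-way ANOVA test".
- Binary outcome: "The study should also have adequate power to detect a binary outcome of clinically meaningful improvement (≥30% from baseline"), or a fall of at least 16.8 FIQR points. No power figure, response rates or SD in points accompany this.
- Analysis: "we will also examine the proportion of participants who show clinical response", using a mixed model with logit link, alongside the continuous FIQR score.

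**The concern.** The continuous comparison is sized to reach 80% and no more. A responder indicator made from the same change scores discards information, so at the same sample size and the same assumed effects it must have less power. The article nevertheless tells the reader that power for the responder outcome is adequate. The only numerical standard for adequacy that it offers is its own 80%.

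At stake is how the responder result will be read. If adequate power is on record, a non-significant difference in response proportions invites the reading that light gives no patient-level benefit. At the planned effect, such a result would be common.

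**Working it through.** **Inputs from the article:** 103 per arm; standardized mean changes 0.47, 0.16 and 0.05; two-sided 0.05; 1:1:1 allocation; response threshold of 16.8 points. **Assumed here:** change scores roughly normal with a common SD (set to 1); SD in points of 12 to 24; pairwise tests at two-sided 0.05 without multiplicity adjustment.

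**1. Reproduce the 80%.** The mean of the three effects is 0.2267. The squared deviations are 0.0592, 0.0044 and 0.0312, with sum 0.0949. The noncentrality is λ = 103 × 0.0949 = 9.77. A noncentral F with 2 and 306 df gives power 80.2%. With 102 per arm it is 79.8%, so 103 is the smallest number that reaches 80%.

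**2. General bound.** For normal data and small effects, a single cut keeps at most 2/π = 0.637 of the information. So λ ≤ 9.77 × 0.637 = 6.22, and a noncentral chi-square with 2 df gives about 60%.

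**3. Search over all cut-offs.** For cut-off c in SD units, P(response) = Φ(m − c), where m is the arm's mean change.

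- *Three-group test.* The best cut-off is c = 0.35, with response rates 54.8%, 42.5% and 38.2% (mean 45.15%). λ = 103 × (0.0963² + 0.0268² + 0.0694²) / (0.4515 × 0.5485) = 6.16, power **59.6%**.
- *Light vs TAU.* The best cut-off is c = 0.26, with rates 58.3% and 41.7%. The difference is 0.1663, with SE 0.0697 under the null and 0.0687 under the alternative. Power = Φ[(0.1663 − 1.96 × 0.0697) / 0.0687] = Φ(0.43) = **66.8%**.
- *Light vs sleep stabilization.* The best cut-off is about c = 0.315, with rates 56.2% and 43.8%. Power = Φ[(0.1232 − 1.96 × 0.0697) / 0.0691] = Φ(−0.19) = **42.3%**.

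For comparison, the same pairs on the continuous scale have Φ(0.42 × √51.5 − 1.97) = 85% and Φ(0.31 × √51.5 − 1.97) = 60%. The low figure for light vs stabilization therefore comes partly from the small assumed difference and partly from the dichotomy.

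These ceilings need neither an SD in points nor a baseline distribution.

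**4. At the 16.8-point threshold** (c = 16.8 / SD):

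| Assumed SD of change | Response rates, light / stabilization / TAU | Three-group power | Light vs TAU |
|---|---|---|---|
| 12 | 17.6% / 10.7% / 8.9% | 42% | 46% |
| 18 | 32.2% / 22.0% / 18.9% | 54% | 59% |
| 24 | 40.9% / 29.5% / 25.8% | 58% | 64% |

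The upper SD is close to 11.2 / 0.47 = 23.8, which would apply if the mean FIQR decrease of 11.2 in the earlier 60-person trial (Introduction) corresponds to the 0.47 effect. That link is an assumption.

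**5. The rule as written.** The threshold actually varies with baseline, because either 30% or 16.8 points suffices. Simulation with assumed baselines (FIQR 31 or more, mean 50 to 60, SD 12 to 15, baseline-change correlation 0 or 0.3) and SD of change 12 to 28 gave 44% to 61% for the three-group test and 48% to 68% for light vs TAU. The rule does not restore 80%.

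**6. Size needed.** At the best cut-off, 80% takes about 162 per arm for the three-group test or 141 for light vs TAU. With no attrition (390 / 3 = 130 per arm) the ceilings are 70% and 77%.

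**The case against.** Several points on the other side stand, and they limit the claim.

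- **Distribution.** The 2/π bound is a result for normal data, and the article states no distribution. Heavier tails raise the three-group ceiling to 71% (logistic), 78% (t with 5 df) or 94% (Laplace). So the claim cannot be called false under every distribution. The article assumes no such shape, however, and its stated 80% reproduces on the ordinary normal basis.
- **Which test.** A reader might infer that no comparison can exceed 60%, or that any responder test misses the planned effect four times in ten. That holds only for the three-group test. The planned model takes TAU as referent, and for light vs TAU the ceiling is 67%, a miss rate of about one in three at best.
- **Undefined term.** The article does not say what adequate means, and a condensed article may leave assumed response rates to the full protocol. The missing calculation is therefore not the fault. The fault is an affirmative statement that the paragraph's own inputs do not support.
- **Role.** The responder proportion is examined in addition to the continuous FIQR, and the article does not say that a null responder result counts against benefit. This limits the harm but does not make the sentence right.

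Two stronger readings are not supported. A reader might blame the either-or definition for the low power. It moves power by only a few points, mostly upward; the loss comes from dichotomizing, and accepting either threshold is a legitimate choice. A reader might also see a contradiction with "14% reduction in baseline Fibromyalgia Impact Questionnaire" in the Introduction, but that describes an earlier study's result and is not a response criterion of this trial.

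**Conclusion.** The concern holds in a limited form. With the article's own sample size and effects, and roughly normal change scores, the binary response falls short of the 80% to which the trial is sized. The ceiling is about 60% for the three-group test, 67% for light vs TAU and 42% for light vs sleep stabilization. At the 16.8-point threshold the three-group figure is about 42% to 58% over the assumed SD range.

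No single replacement figure can be read from the article, because power at a fixed threshold depends on an SD that it does not give. The calculation covers baseline to post-treatment, which is the sizing basis. Any gain from also modelling the 3-month visit is neither claimed nor quantified there. The printed 80% for the continuous outcome is correct.

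**What to change.** Remove the statement that power for the binary outcome is adequate. In its place, give the calculated power for each contrast, with the assumed response rates and SD of change. Under normal changes this is at most about 60% for the three-group test and about 67% for light vs TAU. If the sponsor expects a non-normal distribution that supports a higher figure, state it with its basis. Label the responder analysis supportive, so that a non-significant result is not read as evidence against benefit.

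The cost is a few lines of text and a less favourable stated power. Neither the sample size nor the primary analysis needs to change.
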